## Abstract

**Background:**

Self-tests are available to consumers for more than 25 conditions, ranging from infectious diseases to cardiovascular risk factors. Self-tests are defined as in-vitro tests on body materials such as blood, urine, faeces, or saliva that are initiated by consumers to diagnose a particular disorder or risk factor without involving a medical professional. In 2006, 16% of a sample of Dutch Internet users had ever used at least one self-test and 17% intended to use a self-test in the future. The objectives of this study are to determine (1) the frequency of self-test use, (2) the consumers' reasons for using or not using a self-test, (3) the information that is used by self-testers in the different self-test stages and the consumers' interpretation of the quality of this information, (4) the consumers' response to self-test results in terms of their confidence in the result, reassurance by the test result, and follow-up behaviour, (5) the information consumers report to need in the decision making process of using or not using a self-test, and in further management on the basis of the self-test result, and (6) the quality of the currently available consumer information on a selected set of self-tests.

**Methods:**

Mixed methods study with (1) a cross-sectional study consisting of a two-phase Internet-questionnaire, (2) semi-structured interviews with self-testers and consumers who intend to use a self-test, and (3) the assessment of the quality of consumer information of self-tests. The Health Belief Model and the Theory of Planned Behaviour will serve as the theoretical basis for the questionnaires and the interview topic guides.

**Conclusions:**

The self-testing area is still in a state of flux and therefore it is expected that self-test use will increase in the future. To the best of our knowledge, this is the first study which combines quantitative and qualitative research to identify consumers' information needs and use concerning self-testing, and the consumers' actual follow-up behaviour based on the self-test result, and simultaneously investigates the quality of the currently available consumer information. The results of this study will be used as an input in developing consumer information on self-testing.

## Background

A range of self-tests has become available to consumers in the Netherlands and elsewhere [1]. Self-tests are currently available for more than 25 conditions, ranging from infectious diseases to cardiovascular risk factors. Self-tests are not rarely used; 16% of a sample of Dutch Internet users indicated they had ever used at least one self-test in 2006, whereas 17% of those who had never used a self-test indicated they would probably or definitely use one in the future. The five most frequently used self-tests were tests for diabetes, cholesterol, allergies, urinary tract infection, and HIV [1].

We defined self-tests as in-vitro tests on body materials such as blood, urine, faeces, or saliva that are initiated by consumers to diagnose a particular disorder or risk factor. In other words, by using a self-test, consumers completely avoid the traditional health care systems. Pregnancy tests, home blood-pressure meters, and monitoring tests, e.g. serum glucose for patients with diabetes mellitus to follow-up on their disease and therapy, are examples of tests that are excluded by this definition. Self-tests can be subdivided into four distinct types that are directly accessible to consumers without the need for a preceding consultation with a doctor [1]. The first type of self-test concern self-tests for home use or the over-the-counter tests, in which the consumer is responsible for the execution and interpretation of the test as well as their follow-up behaviour. The second type of self-test comprises self-tests that are offered by an organization which carries out the test in public areas such as local supermarkets and the results are presented immediately. These tests are the so-called street-corner tests like the national cholesterol test offered by the Dutch Heart Association [2]. The third and fourth self-test categories include tests in which a consumer attends a laboratory facility to have body material taken (direct-access laboratory test) or sends body material to a laboratory where the test is executed (home-collect test), after which the result is sent to them by mail or via the Internet.

Four separate phases can be distinguished within the self-test procedure, namely (1) the decision process preceding the performance of a self-test, (2) the actual execution of the self-test (only applicable to over-the-counter tests), (3) the interpretation of the test-result, and (4) the consumers' follow-up behaviour based on the test-result.

In line with the current views on patient autonomy and self-management, self-diagnosis and self-testing can be used as a tool to take responsibility for one's own health [3,4]
. However, the value of self-tests is heavily debated in the scientific literature. Proponents argue that self-testing increases testing rates, resulting in more timely diagnosis and treatment; self-testing is convenient and provides anonymity, and it promotes patient empowerment [5-8]. Opponents hold that at-risk populations do not use self-tests, self-tests entail relatively high costs, and testing without consulting a physician may result in adverse medical or psychological outcomes [5-7]. In view of this debate, effective consumer education seems essential in this new area, as self-tests are likely to become even more easily available and more widely used [1,3]. To the best of our knowledge, however, this is the first study to combine quantitative and qualitative research to identify consumers' information needs and use related to self-testing, and the consumers' actual follow-up behaviour based on the self-test result, and at the same time investigates the quality of the currently available consumer information. This study aims to identify potential problems and benefits with self-test use and to explore the impact of self-testing for health-care use. Furthermore, the results will be used as an input for a follow-up study which is aimed at the development of consumer information, including a decision aid, for self-testing. By developing new consumer information for self-testing, we aim to provide consumers with a basis for a deliberate and informed choice.

### Theoretical framework

The Health Belief Model (HBM) [9] as well as the Theory of Planned Behaviour (TPB) [10] will be used as the theoretical framework in constructing the questionnaires (Study 1) and the interview topic guides (Study 2). The HBM was originally designed to explain health behaviours, such as screening, which may be comparable to self-testing. Nowadays the model has been used to explain and predict a wide variety of health-related behaviours (e.g. diabetes self-care, alcohol consumption, and smoking) [9,11,12]. The HBM is based on psychological expectancy-value models which state that human behaviour is the result of the valence that an individual relates to a specific goal and on the individual's assessment that a certain action will accomplish that goal. The HBM hypothesizes that health-related behaviour is the result of the individual's appraisal of the susceptibility to and the severity of a certain condition or illness and the individual's belief that a specific health action would result in a decrease of the susceptibility to or the severity of that condition. However, the health-related behaviour will only be performed if perceived barriers to that behaviour are compensated by the perceived benefits of performing it. Additionally, action is more likely to be initiated if cues (e.g. bodily or environmental events) are available and if the person has a high level of self-efficacy; e.g. if the person is confident that he or she is able to perform that action [9,11,13]
.

Although the HBM and the TPB partially overlap, the TPB adds some important concepts to the HBM. According to the TPB [10], intention is the most proximal determinant of behaviour. Intention, in turn, is determined by three constructs which are conceptually independent: attitude, subjective norms, and perceived behavioural control. Attitude is based on an evaluation of the individual's positive and negative beliefs about consequences of that behaviour [10]. Subjective norms represent the idea that important others approve or disapprove of the person performing that behaviour. Perceived behavioural control is approximately similar to the self-efficacy concept of the HBM which comprises the individual's belief that (s)he is able to successfully perform the behaviour [9,12]. According to the TPB, perceived behavioural control influences behaviour both directly and indirectly, through intention [14]. The HBM as well as the TPB have shown to successfully explain several health-related behaviours [9,11,12,15-17].

### Study aim and research questions

The present study aims to validate the 2006 findings on frequency in self-test use, to describe information needs and information use of self-testers and non-testers, as well as the self-testers' further management on the basis of the test result. Furthermore, the quality of the existing consumer information for the most frequently used self-tests will be described.

This study will investigate the following research questions:

1. What is the frequency of self-test use?

2. What are the consumers' reasons for using or not using a self-test?

3. What information do self-testers use in the different self-test stages and what is the consumers' interpretation of the quality of this information?

4. What is the consumers' response to self-test results in terms of their confidence in the result, reassurance by the test result, and follow-up behaviour?

5. What information do consumers need in the decision making process of using a self-test or not using a self-test, and in further management on the basis of the self-test result?

6. What is the quality of the currently available consumer information on a selected set of self-tests?

## Methods

### Study design

Mixed methods study with (1) a cross-sectional study consisting of a two-phase Internet-questionnaire, (2) semi-structured interviews with self-testers and consumers who intend to perform a self-test, and (3) the assessment of the quality of consumer information accompanying self-tests.

### Ethical approval

The Medical Ethical Committee of Maastricht University indicated that no ethical approval was needed for this study.

### Study 1: Cross-sectional study

#### Aim

The aim of this cross-sectional study is to answer research questions (1) what is the frequency of self-test use?, (2) what are the consumers' reasons for using or not using a self-test?, (3) what information do self-testers use in the different self-test stages and what is the consumers' interpretation of the quality of this information?, and (4) what is the consumers' response to self-test results in terms of their confidence in the result, reassurance by the test result, and follow-up behaviour?

#### Selection criteria

Individuals aged 12 years or older who have an e-mail address will be randomly selected from the Flycatcher Internet-panel.

#### Methods of data collection

The survey will be conducted by Flycatcher, a Dutch ISO-certified institute for online research (ISO 26361 and ISO 20252), which will handle the recruitment of participants and the distribution of the questionnaires. Individuals aged 12 years or older who have an e-mail address can apply for the Flycatcher Internet-panel by registering at the Flycatcher website http://www.flycatcher.eu. New panellists are recruited through various channels: e.g. 'send-to-a-friend' actions by existing panel members, newsletters, directories of third parties (after permission), other private panels (after permission), and word-of-mouth advertising. Panellists are invited by e-mail to participate in a survey. This e-mail contains a short description of the study and an expiration date for filling out the survey. Panellists receive a gift voucher when they have completed a certain number of questionnaires.

In this survey, two consecutive questionnaires will be used. The first questionnaire will be based on the questionnaire that was used in the 2006 study to identify the use of self-tests [1]. This questionnaire will be sent to approximately 6,500 panellists and will determine the prevalence of and intention to use self-tests, types of self-tests used, and a number of demographic and lifestyle characteristics of participants (e.g. gender, age, level of education, perceived health status). The second questionnaire will be based on results of the 2006 study [1,18], and on consensus among the research team. This questionnaire will be sent to a selection of self-testers and will determine the information needs and information use, the consumers' interpretation of the quality of this information, the consumers' confidence in and their reassurance by the test-result, and their follow-up behaviour. Both questionnaires will be piloted in a small sample of the target population before being distributed on the Internet. The questionnaire will start with a short introduction of the purpose of the study and will provide a definition of self-testing with examples of what is considered a self-test and what is not. Finally, consent for recontacting respondents for further participation in the study will be asked. After one week, one reminder will be sent to non-responders. Both questionnaires are available as additional files 1 and 2.

#### Justification of sample size

Results of the 2006 study indicated that 16% of respondents had used a self-test. Based on Flycatcher's previous experiences we expect a response rate of 60%. The survey will be sent to 6500 respondents, which will result in a response of 3900 respondents and will include approximately 700 self-testers and 3200 non-testers.

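### Study 1 sample size: the stated split of 700 to 3200 does not follow from 6500 invitations, 60% response and 16% use, which give 624 and 3276

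*Protocol article*

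**What the plan says.** All the inputs stand in the protocol article, Study 1, under the heading on justification of sample size.

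- Prevalence: "Results of the 2006 study indicated that 16% of respondents had used a self-test". The Abstract and Background give the same 16%.
- Invitations: "The survey will be sent to 6500 respondents". The Study 1 data collection section agrees: "This questionnaire will be sent to approximately 6,500 panellists".
- Response: "we expect a response rate of 60"%, based on the research institute's experience.
- Total: "which will result in a response of 3900 respondents".
- Split: the survey "will include approximately 700 self-testers and 3200 non-testers".

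No other prevalence is given as a planning value. The Abstract says that "it is expected that self-test use will increase in the future", and the Discussion says much the same, but neither gives a figure or links the expectation to the sample size.

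**The concern.** The paragraph prints its inputs and its result together, and the two disagree. The total follows from the inputs but the division into testers and non-testers does not.

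This is the only sample size statement for Study 1. Self-testers are the smaller group and the one that later steps draw on: the second questionnaire goes to a selection of them, and the tester interviews in Study 2 recruit from those who agree to be contacted again. A reader judging whether the survey will find enough self-testers would rely on 700.

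Prevalence of use is also what research question 1 estimates, and the study aim includes validating the 2006 frequency. A planning prevalence other than the 2006 value should therefore be visible to the reader.

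**Working it through.** **1. The plan's total.** Respondents = invitations x response rate = 6500 x 0.60 = 3900. This reproduces the stated figure exactly.

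**2. The split at the stated prevalence.**
- Self-testers = 3900 x 0.16 = 624, against 700 stated. Difference: 700 - 624 = 76, which is 76/700 = 10.9% of the stated figure, or 76/624 = 12.2% above the derived one.
- Non-testers = 3900 x 0.84 = 3276, against 3200 stated. Difference: 76/3200 = 2.4%, so this figure taken alone is close.

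**3. Could rounding explain it?**
- Rounding the results: to the nearest hundred, 624 and 3276 become 600 and 3300, not 700 and 3200.
- Rounding the prevalence: if 16% stands for anything up to 16.5%, the most it gives is 3900 x 0.165 = 643.5, still 600 to the nearest hundred.
- Rounding the response rate: this cannot help, because the paragraph fixes the total at 3900, and 700 + 3200 = 3900.

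**4. What the stated pair implies.**
- Implied prevalence = 700/3900 = 17.9%. At 18%: 3900 x 0.18 = 702 and 3900 x 0.82 = 3198, which matches both figures.
- If both figures are rounded to the nearest hundred, self-testers could lie between 650 and 750, a prevalence of 650/3900 = 16.7% to 750/3900 = 19.2%. The whole range lies above 16%.
- Keeping 16%, 700 self-testers need 700/0.16 = 4375 respondents. That means a response of 4375/6500 = 67%, or 4375/0.60 = about 7292 invitations.

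**5. What the difference does to precision.** Worst-case 95% half-width for a proportion among self-testers, 1.96 x sqrt(0.25/n), if all of them answer:
- n = 700: 3.7 points
- n = 624: 3.9 points

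**6. Does any later number use 700?** The second questionnaire is given no target count. In Study 2, the 100 self-testers to be approached come from 20 per test x 5 tests, and the 60 intending users from 30 per test x 2 tests. Replacing 700 by 624 changes none of these.

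**The case against.** The strongest defence is that 16% is reported as a 2006 result and is not expressly called the planning assumption. The Discussion describes free test offers and partial reimbursement by insurers since 2006 and expects wider use. A planning value near 18% would fit that account and would reproduce the printed pair. This stands as a plausible explanation, and an omitted assumption is at least as likely as a slip in calculation. It does not rescue the sentence, because 16% is the only prevalence offered there and the expected growth is neither quantified nor tied to the sample size.

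A second defence is that little depends on the figure. This stands. The Study 1 analysis is descriptive, and the article ties no power or precision target to 700. The number is a forecast, not a requirement that 624 would fail to meet.

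A reader might go further and infer that every downstream yield is overstated, or that the interviews will fall short. The article does not support either. The Study 2 counts are built per test and not from 700. The interview filters (consent to further contact, a recent top-five test or the intention to do one, travel distance) are given without rates, so no shortfall can be calculated.

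**Conclusion.** The expected yield is inconsistent with the inputs printed beside it. At 6500 invitations, 60% response and 16% use, it is 624 self-testers and 3276 non-testers; the stated pair needs about 18%.

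The shortfall of 76 self-testers (11%) holds only if 16% is the planning value. If about 18% was intended, the counts are right and what is missing is the assumption. The article does not settle which, so it would be wrong to conclude that the authors miscalculated. Under either reading the sentence needs correcting.

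Severity is minor. The total of 3900, which governs precision for the frequency of use, is correct. Precision among testers changes by about 0.2 points, and no design choice or later count changes.

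**What to change.** Reconcile the one sentence in either of two ways:

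- keep 16% and restate the yield as about 620 self-testers and 3,280 non-testers; or
- keep 700 and 3200, and state and justify the prevalence of roughly 18% that they assume.

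The cost is one sentence. Under the first option the stated tester yield becomes slightly less favourable; under the second, one assumption is added. Neither changes the number of invitations, the questionnaires or the interview numbers.

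As an optional addition, not needed to correct the error, the paragraph could give the precision for research question 1: with 3900 respondents and 16% use, 1.96 x sqrt(0.16 x 0.84/3900) = 1.15 points either side.

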#### Methods of data analysis

Analysis will be performed by using SPSS 16.0. Basic descriptive statistics will be used to describe the respondents' socio-demographic and lifestyle characteristics, the frequency of self-test use, their information use and information needs during the different self-test phases, the degree of consumer confidence in and reassurance by the test-result, and their follow-up behaviour.

### Study 2: Semi-structured interviews

#### Aim

The purpose of the semi-structured interviews will be to gain more in-depth understanding of consumers' considerations about self-testing. More specifically, we aim to answer research questions (2) what are the consumers' reasons for using or not using a self-test?, (3) what information do self-testers use in the different self-test stages and what is the consumers' interpretation of the quality of this information?, (4) what is the consumers' response to self-test results in terms of their confidence in the result, reassurance by the test result, and follow-up behaviour?, and (5) what information do consumers need in the decision making process of using a self-test or not using a self-test, and in further management on the basis of the self-test result?

#### Selection criteria

Individuals who indicate in the Internet survey that they are willing to be recontacted for participating in a face-to-face interview, will be approached. From this selection, individuals will be contacted if they performed a top-five most frequently used self-test within the last two years or intend to perform such a test, and live within a two-hour drive radius. We will purposively sample consumers with regard to gender, age, and level of education.

#### Methods of data collection

Semi-structured interviews will be held in order to explore the considerations of self-testers and consumers who intend to perform a self-test about using or potentially using a self-test. Respondents will be approached by e-mail that provides a short introduction of the research team and the research project, a description of the purpose of the interview, the duration of the interview and the incentive that participants will receive (€25 for a 1-hour interview). Furthermore, individuals will be asked to provide their name and phone number by e-mail if they are willing to participate in an interview. The researchers will contact them by phone to schedule an appointment for the interview. A semi-structured topic guide will be used for the interviews in which the reasons to use a self-test, the user-friendliness of the test, the interpretation and perceived reliability of the test result, the information needs and use, and follow-up actions based on the test result will be addressed. Interviews will be held at the homes of the participants. At least 8 participants per test will be interviewed and in case data-saturation is not met, additional participants will be invited for an interview. All interviews concerning a particular test will be held by one researcher (JG, MI, or a medical student) and will be audio-taped. The semi-structured topic guides for testers and consumers who intent to perform a self-test are available as additional files 3 and 4.

#### Justification of sample size

Assuming that 50% of respondents who have used a self-test and 25% of respondents who intend to use a self-test respond to the invitation to take part in an interview, we will need to approach 100 self-testers in total (20 persons per test divided over 5 tests) and 60 respondents who intend to use a self-test to take part in the interviews (30 persons per test divided over 2 tests).

